## Abstract

**Background:**

Time-restricted eating (TRE) has been shown to be associated with improvements in some aspects of the metabolic syndrome. Nevertheless, only a few studies have addressed the effect of TRE on pulse wave velocity (PWV). We thus propose a randomized controlled trial to compare the effects of TRE with standard dietary advice on PWV and thereby present the protocol.

**Methods:**

Forty-eight participants will be assigned to either TRE or control groups using simple randomization. The TRE group will consume their meals during a 10-h period and experience 14 h of fasting. They will also be advised to consume their last meal no later than 20:00. Both groups will receive standard dietary advice. The participants will be followed for 6 weeks. The primary outcome will be changes in PWV. Laboratory measurements, including lipid profile, liver enzyme tests, fasting blood glucose (FBG), insulin concentrations, and insulin resistance, as well as anthropometric data, blood pressure, basal metabolic rate, appetite status, physical activity level, sleep quality, cognitive function, quality of life, and calorie intake, will be evaluated throughout the study.

**Discussion:**

The outcomes of this study will allow a comparison of the effects of TRE and standard dietary recommendations on PWV and other cardiometabolic factors in individuals with metabolic syndrome (MetS).

**Trial registration:**

Iranian Registry of Clinical Trials; code: IRCT20201230049889N1; registered on August 14, 2022. The registration of the trial is accessible at: https://www.IRCT.ir/trial/64485?revision=281341.

## Introduction

### Background and rationale {6a}

Metabolic syndrome (MetS) is a set of simultaneous systemic abnormalities associated with increased risk for cardiovascular diseases (CVD) that was first introduced and discussed in the literature about three decades ago. Based on the International Diabetes Federation (IDF), MetS is defined as the presence of central obesity plus at least two other risk factors, including hyperglycemia, hypertriglyceridemia, low high-density lipoprotein (HDL), and hypertension [1]. Insulin resistance, which is believed to be the main mechanism driving MetS, increases the risk of type II diabetes mellitus (T2DM), CVD, and other diseases [2].

The global increase in the prevalence of MetS due to inactivity and obesity and its relationship with T2DM and CVD has become a subject of interest for researchers aiming to reduce the burden of MetS in both clinical and social settings [1, 2]. Scuteri et al. concluded that the pattern of MetS components differed between countries and cultures, and thus treatment approaches may need to also vary depending on the population [3].

The global prevalence of MetS is 20–25% [4, 5], while a meta-analysis of 69 Iranian studies over a period of 17 years reported that one third of Iranian adults had MetS. Prevalence varied by age and sex such that, in people under 40, males were prominently affected, whereas MetS prevalence was higher among postmenopausal women compared to age-matched men [6]. Furthermore, the patterns of MetS components differ between men and women [7]. Notably, MetS is more strongly associated with an increased risk for coronary heart disease (CHD) and CVD in women [8].

Nutrition, in terms of both quantity, quality, and timing of food intake, plays an important role in MetS development [9]. The suggested mechanism linking metabolic disease with meal irregularity is through effects on the circadian rhythm since food acts as a “zeitgeber,” i.e., “time keeper” [10]. The desynchronization of circadian rhythm due to irregular eating patterns causes lipid metabolism impairment, glucose intolerance, insulin insensitivity, and activation of inflammatory cascades [11]. Moreover, the insulin resistance resulting from meal irregularity activates several mechanisms associated with atherosclerosis. Insulin resistance leads to dyslipidemia, inflammation, and endothelial dysfunction, thereby increasing the risk of atherosclerosis [12]. In this regard, a link can be established between both meal irregularity and metabolic syndrome with arterial stiffness.

The effect of time-restricted eating (TRE) on MetS has been documented in several animal and human studies. It has been proposed that TRE can improve insulin insensitivity [13]. Furthermore, research has reported that TRE may lead to a reduction in body weight and blood pressure, as well as improvements in body composition, and lipid and glucose metabolic profiles [11]. TRE appears to be a safe intervention, with minimal adverse events reported in studies [14].

The cardiometabolic effects of TRE have also been investigated. A trial showed that a 12-week 10-h TRE significantly improved cardiometabolic indices in 12 individuals with MetS [15]. Zuo et al. conducted a study investigating the effects of a high-protein, intermittent fasting low-calorie (HP-IF-LC) diet on obese individuals. During the 12-week weight loss phase (first phase) of the study, they found a significant decrease in pulse wave velocity (PWV). In the 1-year weight maintenance phase (second phase) of the study, they compared a high-protein, intermittent fasting (HP-IF) diet with a heart healthy (HH) diet and observed a significant decrease in PWV [16]. A systematic review also found that Ramadan fasting, which involves restricting food and drink intake to a specific window between sunrise and sunset, improved lipid profile and anthropometric features in healthy individuals but not in diabetic individuals [17]. In another study, participants followed early time-restricted feeding (eTRF) with an eating window of 6 h compared to a 12-h eating period for 5 weeks. Eight overweight prediabetic males were assigned to intervention and control groups. The eTRF led to significant reductions in systolic and diastolic blood pressure, fasting insulin level, mean insulin level, and peak insulin value. They observed an improvement in PWV and augmentation index (AIx), although not statistically significant [13].

However, to the best of our knowledge, studies did not evaluate the effect of TRE alone on arterial stiffness, and some assessed the effects of TRE in populations other than individuals with MetS. A meta-analysis in 2020 suggested that despite the observed benefits of TRE in literature, randomized controlled trials (RCT) with larger sample sizes are necessary to further support the usefulness of TRE in prevention and treatment of MetS [11].

The proposed study aims to recruit a larger number of participants to assess the effect of a 6-week 10-h TRE protocol on PWV in individuals with MetS. Other cardiometabolic effects of TRE will also be investigated. It is hypothesized that TRE will reduce PWV, a marker of arterial stiffness, and improve the cardiometabolic profile in individuals with MetS. Considering the sex-related differences in MetS components and the potential effect of the menstrual cycle on metabolism, this study limits recruitment to men. With this approach, we will have a homogeneous group, which will reduce variability and minimize the confounding factors, leading to more robust results. Also, taking into account that the relationship between unhealthy lifestyles and MetS is stronger in men than in women [18], focusing this study on men may help develop gender-specific prevention and intervention programs.

## Objectives {7}

### Primary objectives

The primary objective is to determine the effect of a 10-h TRE compared to standard dietary recommendations on indices of arterial stiffness among men with MetS.

### Secondary objectives

The secondary objective is to determine the effect of 10-h TRE compared to standard dietary recommendations on:Anthropometric parameters and body composition outcomes assessed by bioelectrical impedance analysis (BIA)Energy metabolism outcomes assessed by indirect calorimetry (IC)Blood markers including lipid profile (triglyceride, total cholesterol, low-density lipoprotein (LDL), and high-density lipoprotein (HDL)), liver enzyme tests (aspartate aminotransferase (AST), alanine aminotransferase (ALT), and alkaline phosphatase (ALP)), fasting blood glucose (FBG), and insulin concentrationsInsulin resistance assessed by the Homeostatic Model Assessment for Insulin Resistance (HOMA-IR) [19]Appetite status outcomes assessed by visual analog scale (VAS)Cognitive function outcomes assessed by the Go-No-Go (GNG) test and the Wisconsin Card Sorting Test (WCST)Quality of life outcomes assessed by the World Health Organization Quality of Life Brief Version questionnaire (WHOQOL-BREF*)*Sleep quality outcomes assessed by the Pittsburgh Sleep Quality Index (PSQI)Physical activity outcomes assessed by the International Physical Activity Questionnaire (IPAQ) and pedometerCalorie intake assessed by 3-day food and drink diary

## Trial design {8}

This study is designed as a randomized controlled trial (RCT), with parallel groups and an allocation ratio of 1:1, in a superiority design framework. Regarding the allocation of each participant to the control and intervention groups, randomization will be run using computerized random number generation and sealed envelopes will be used to conceal the random allocation. The potential participants will be identified among the population of the PERSIAN Cohort Study in Mashhad University of Medical Sciences and will be recruited through phone calls. Screening, including both physical and laboratory examinations, will be carried out to assess the presence of MetS based on IDF criteria [16]. The study design and planned assessments for each stage of the study are explained in detail, in the following sections, and briefly summarized in Table 1. The study protocol adheres to the checklist of the Standard Protocol Items: Recommendations for Interventional Trials (SPIRIT) guidance (Table 1).

**Table 1 Tab1:** The timeline for the enrollment, intervention, and assessment schedule

	**Timepoint**	**Timeline**				
		**Enrollment**	**Allocation**	**Study period**		
				**Day 1**	**Week 3**	**Week 6**
	**Enrollment**	✔				
	**Eligibility screening**	✔				
	**Informed consent**		✔			
	**Allocation**		✔			
	**Intervention**					
	Intervention group: 10-h TRE					
	Control group: non-TRE					
**Fasting state assessments**	**Anthropometry**			✔	✔	✔
	**Bioelectrical impedance analysis**			✔	✔	✔
	**Pulse wave velocity**			✔	✔	✔
	**Indirect calorimetry**			✔		✔
	**Blood laboratory tests**					
	• Lipid profile: TG, TC, LDL, HDL			✔	✔	✔
	• Blood glucose			✔	✔	✔
	• Insulin concentration			✔	✔	✔
	• HOMA-IR			✔	✔	✔
	• CBC			✔		✔
	• hs-CRP			✔		✔
	• Liver enzymes: AST, ALT, ALP			✔		✔
	**Appetite VAS** (pre-prandial)			✔		✔
	**Breakfast (standard meal)**			✔		✔
**Post-prandial state assessments**	**Appetite VAS** (post-prandial)			✔		✔
	**Blood laboratory tests**					
	**1st hour post-prandial**					
	• Blood glucose			✔		✔
	• Insulin concentration			✔		✔
	**2nd hour post-prandial**					
	• Blood glucose			✔		✔
	• Insulin concentration			✔		✔
	• CBC			✔		✔
	• hs-CRP			✔		✔
	**Cognitive function tests**					
	Go-No-Go test			✔		✔
	Wisconsin Card Sorting Test			✔		✔
	**WHOQOL-BREF questionnaire**			✔		✔
	**PSQI questionnaire**			✔		✔
	**IPAQ**			✔		✔
	**Pedometer*******			a		b
	**Three-day food and drink diary**^**†**^			c	c	c

*Abbreviations*: *TRE*, time-restricted eating; *TG*, triglyceride; *TC*, total cholesterol; *LDL*, low-density lipoprotein; *HDL*, high-density lipoprotein; *HOMA-IR*, Homeostatic Model Assessment for Insulin Resistance; *CBC*, complete blood count; *hs-CRP*, high-sensitivity C-reactive protein; *AST*, aspartate aminotransferase; *ALT*, alanine aminotransferase; *ALP*, alkaline phosphatase; *VAS*, visual analog scale; *WHOQOL­BREF*, World Health Organization Quality of Life Brief Version; *PSQI*, Pittsburgh Sleep Quality Index; *IPAQ*, International Physical Activity Questionnaire

^*^Pedometer: daily evaluation, in the first 7 days and the last 7 days of the study period

^a^Throughout week 1

^b^Throughout week 6

^†^Three-day food and drink diary: daily evaluation

^c^Three consecutive days in weeks 1, 3, and 6

## Methods: participants, interventions, and outcomes

### Study setting {9}

This study will be conducted at the center of the PERSIAN Cohort Study at Mashhad University of Medical Sciences, at Imam Reza Academic Hospital, located in the North-East of Iran.

### Eligibility criteria {10}

#### Inclusion criteria

Participants will be men aged 18 to 65 years old, with documented MetS according to the IDF criteria [20] and a body mass index (BMI) < 35 kg/m^2^.

#### Exclusion criteria

Individuals who fall under the following categories will be excluded from the study: shift workers, individuals consuming food for less than 14 h per day, those with a documented diagnosis of diabetes mellitus, restrictive diets (e.g., cancer patients), thyroid disorders, eating disorders, receiving dietary supplements other than vitamins or minerals, and those unable to adhere to the TRE protocol.

### Who will take informed consent? {26a}

The principal researcher will inform eligible individuals about the study details, providing both written and verbal information in clear and comprehensible language. Subsequently, the interested individuals will be asked to provide written consent, in accordance with the standard procedures of the trial. Those who decline to give written consent or demonstrate significant distress will not be included in the study. In the case of illiterate individuals, since our study includes tests requiring literacy, it is not possible to recruit them.

### Additional consent provisions for collection and use of participant data and biological specimens {26b}

The consent form outlines the terms for data usage in case of participant withdrawal from the study and grants permission for sharing relevant data with specific academic experts or other regulatory authorities (ethics number: IR.MUMS.MEDICAL.REC.1401.213).

## Interventions

### Explanation for the choice of comparators {6b}

This study aims to evaluate the pure effects of TRE intervention on arterial stiffness indices. The comparison will be between the TRE group and the control group.

To mitigate the risk of contamination in TRE trials, where control group participants may adjust their eating times to mimic the intervention group, we emphasize the importance of maintaining their usual eating window and closely monitor their adherence to align with their designated group. Also, we planned to employ the appropriate statistical methods to assess and adjust the potential impact of contamination, as explained in the “Statistical methods” section.

### Intervention description {11a}

#### Intervention group (10-h TRE)

The participants will be instructed to limit all energy intake to a self-selected eating window of 10 h/day, with advice to consume the last meal no later than 20:00. Participants will choose the most suitable 10-h eating window with the researchers’ assistance. They will be free to consume non-energy-containing beverages during their fasting period. To avoid interfering with the participants’ sleep quality, they will be advised to avoid consuming tea and coffee after 20:00. Although no individualized instructions will be provided on dietary intake, participants will receive verbal recommendations and written healthy eating guidelines [21].

#### Control group (non-TRE)

The participants will not be instructed to limit their eating window. While no individualized dietary plans will be provided, participants will receive verbal recommendations and written healthy eating guidelines [21].

All participants will have a 45-min consultation with the study’s nutritionist on day 1 (baseline visit), week 3, and week 6 (final visit). Figure 1 provides a summary of the study protocol.

**Fig. 1 Fig1:**
[figure not shown]
Summary of the study. “*” symbol indicates the following: the assessments of physical activity level (IPAQ), sleep quality (PSQI), cognitive function (GNG and WCST), and quality of life (WHOQOL-BREF) are assigned to this stage. “^†^” symbol indicates the following: *Pedometer* is used for daily physical activity evaluation, during the first 7 days and the last 7 days of the study period, throughout weeks 1 and 6. ^“‡^” symbol indicates the following: *Three-day food and drink diary* is used to record calorie intake for three consecutive days in weeks 1, 3, and 6. Abbreviations: *TRE*, time-restricted eating; *BIA*, bioelectrical impedance analysis; *PWV*, pulse-wave velocity; *IC*, indirect calorimetry; *VAS*, visual analog scale; *PP*, post-prandial

### Criteria for discontinuing or modifying allocated interventions {11b}

No specific side effects are anticipated following the TRE intervention. The potential reasons for discontinuing the intervention include the occurrence of any adverse effects due to the intervention or measurements or the participant’s unwillingness to continue participation. The Ethics Committee of Mashhad University of Medical Sciences (MUMS) will make decisions regarding the referred cases.

### Strategies to improve adherence to interventions {11c}

Compliance is defined as adhering to the planned 10-h TRE in the intervention group and avoiding eating time restrictions in the control group. Participants will be asked to write down the start and end times of food consumption in the prepared forms, which will allow us to improve adherence and identify any deviations from the prescribed eating window. Also, the participants will be asked to keep a food and drink diary including the time of consumption for 3 consecutive days at weeks 1, 3, and 6. Data collected from the reported 3-day food and drink diary will also be used in analyses. To further increase study compliance, a daily message will be sent to the participants in the TRE group to remind them of their eating window. Those participants who do not respond to 2 messages per week will be followed up by phone call.

### Relevant concomitant care permitted or prohibited during the trial {11d}

This trial allows all concomitant prescribed therapeutic interventions, in relevance to the measured parameters, without any restrictions. However, we will closely monitor for any changes in medications. If a participant needs to make a medication change, we will assess whether they should remain in the study on a case-by-case basis. Any change in medication dose will be considered a potential confounding factor. This approach will help to minimize confounding due to medication use and ensure the validity of our findings.

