## Assignment of interventions: blinding

### Who will be blinded {17a}

The type of intervention does not allow blinding for either participants or field researchers who will provide advice on the type of regimen. The statistical analysis however will be conducted by a blinded statistician, to minimize potential bias in the data analysis.

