## Statistical methods

### Statistical methods for primary and secondary outcomes {20a}

The SPSS software version 20 will be used for data analysis based on the intention-to-treat method. Comparison between groups will be conducted by independent sample *t*-test and Mann-Whitney tests for quantitative data, while within-group comparisons will be assessed using paired sample *t*-test and Wilcoxon signed-rank tests. Comparison between groups will be conducted by chi-square test for qualitative data, and within-group comparisons will be assessed by McNemar’s test. Qualitative data (levels of physical activity based on IPAQ) will be presented using frequencies and percentages, while quantitative data (anthropometric parameters, arterial stiffness indices, indirect calorimetry parameters, laboratory tests, appetite VAS score, GNG score, WCST score, WHOQOL-BREF score, PSQI score, pedometer reports, 3-day food and drink diary reports) will be presented using mean and standard deviation or median and interquartile range depending on the data distribution. The relationship between outcomes will be assessed using Pearson’s correlation coefficient and Spearman’s rank correlation coefficient. A *p*-value of < 0.05 will be considered statistically significant.

To mitigate the risk of contamination in TRE trials, we will conduct sensitivity analyses to assess the impact of potential adjustments in the control group’s eating times. Furthermore, we will compare the results of the intention-to-treat analysis with per-protocol analyses, by checking the consistency of these results. Also, appropriate statistical methods will be employed to predict potential contamination and its impact on the study results.

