### Methods in analysis to handle protocol non-adherence and any statistical methods to handle missing data {20c}

The trial will use an intention-to-treat analysis protocol, to minimize the impact of participant dropouts and non-adherence to the protocol by analyzing all participants according to their original assignment, regardless of whether they completed the study or not. However, missing data from participants who drop out or do not adhere to the protocol will be imputed using statistical methods to ensure that the analysis will not be biased by missing data.

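### Unblinded, criterion-free decisions on whether men with a medication change stay in the study can lose PWV outcomes selectively and conflict with the promised intention-to-treat analysis

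*Protocol article*

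**What the plan says.** In the protocol article, the section on concomitant care {11d} opens permissively: "This trial allows all concomitant prescribed therapeutic interventions, in relevance to the measured parameters, without any restrictions". It then adds a condition for a man whose medication has to change: "we will assess whether they should remain in the study on a case-by-case basis". It calls a dose change a possible confounder and gives the purpose of the rule: "This approach will help to minimize confounding due to medication use and ensure the validity of our findings". It names no criteria and does not say who decides beyond the study team.

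On blinding, {17a} states: "The type of intervention does not allow blinding for either participants or field researchers". Section {17b} confirms that the statistician is the only blinded person. Under {19} the primary investigator collects all data. The Ethics Committee's role in {11b} concerns stopping the intervention for adverse effects or unwillingness; it is not extended to medication changes.

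On analysis, {20a} says: "The SPSS software version 20 will be used for data analysis based on the intention-to-treat method". Section {20c} promises "analyzing all participants according to their original assignment, regardless of whether they completed the study or not", and adds that "missing data from participants who drop out or do not adhere to the protocol will be imputed using statistical methods". No section says whether a man taken out under {11d} is still measured at weeks 3 and 6.

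**The concern.** A medication change after randomisation is not a baseline confounder; randomisation already deals with those. It is an event that the assigned diet may influence. The protocol itself expects TRE to improve lipids, glucose and insulin (Expected outcomes) and notes that PWV depends on blood pressure (Discussion). Whether a man's drugs change can therefore be linked both to his arm and to his PWV. If people who know the arm, and may have seen the measurements, then decide who stays, the men remaining in the two arms may no longer be comparable. The rule could introduce the kind of bias that it is meant to prevent.

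At stake is the primary comparison in a trial of 24 men per arm, where a few lost outcomes matter. A later analysis plan cannot repair this. PWV that was never measured can only be imputed, and the imputation would have to assume that removal is unrelated to the unseen value, given the observed data. The trial could not check that assumption.

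**Working it through.** **1. The passages side by side.** Section {11d} makes staying in the study discretionary after randomisation. Sections {17a} and {17b} leave the decision-makers aware of the arm. Sections {20a} and {20c} commit to analysing all men as assigned, completers or not. The two commitments fit together only if men with a medication change continue to be measured, and no section says that they are.

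**2. The plan's own figure.** Sample size {14} gives alpha 5%, beta 20%, effect size 0.63 and 20 per group. Its second formula reproduces this:

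n = (1.960 + 0.842)² / 0.63² = 7.849 / 0.3969 = 19.8, rounded up to 20.

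The 24 enrolled per group equals 20 × 1.2; dividing by 0.8 would give 25. Comparing the section's two formulas shows that f is the difference divided by √(σ₁² + σ₂²). With equal SDs, the planning effect in SD units is 0.63 × √2 = 0.89.

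**3. Illustration of a possible shift.** The documents give no rate of medication change or removal, so every input here is an assumption: removal in one arm only, of the men with the poorest values on a trigger that has correlation ρ with the PWV change, and no use of the removed men in the analysis. If a fraction p is removed from the upper tail of a standard normal trigger, the mean of those who remain moves by ρ × φ(z) / (1 − p), where z is the cut-off for the upper fraction p.

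- p = 2/24 = 0.083: z = 1.383, φ(z) = 0.153, and 0.153 / 0.917 = 0.167.
- p = 0.15: z = 1.036, φ(z) = 0.233, and 0.233 / 0.85 = 0.274.

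| Removed from one arm | ρ | Shift (SD) | Share of 0.89 SD |
|---|---|---|---|
| 2 of 24 | 0.5 | 0.08 | 9% |
| 2 of 24 | 1.0 | 0.17 | 19% |
| 15% | 0.5 | 0.14 | 15% |
| 15% | 1.0 | 0.27 | 31% |

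**4. Check by simulation.** The setting was 20,000 trials per scenario, 24 men per arm, no true effect, removal from the TRE arm only, and an unpaired t-test.

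- 2 removed: the spurious difference is about 0.05, 0.08 and 0.16 SD at ρ = 0.3, 0.5 and 1.0, with type I error of about 5.4%, 5.7% and 9.5%.
- 4 removed: about 0.09, 0.14 and 0.28 SD, with type I error of about 5.7%, 7.8% and 18.1%.
- ρ = 0: no bias, and type I error stays at about 5%.

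The simulation agrees with the formula. It also shows that the harm depends on how closely removal tracks outcome.

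**The case against.** The strongest reply is that {11d} permits bias but does not show that it will occur. The section does not say why drugs would change or how the team would decide. At moderate correlation with two removals, type I error stays close to nominal. This is fair, and it is why the figures are only an illustration. The rule remains open-ended and arm-aware.

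Several stronger readings are tempting, but the document does not support them.

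- *Removed men are excluded from the analysis.* A reader might infer this from {11d}. Section {20c} keeps everyone in the analysis whether or not they complete, so such men would presumably be imputed. The defect is discretionary loss of outcomes, not a written exclusion.
- *Measured PWV of non-adherent men is overwritten.* A reader might infer this from {20c}, but that sentence concerns missing data, and imputing what is missing is compatible with intention-to-treat. Only the mention of non-adherence leaves a doubt, which a clarification removes.
- *The rules favour TRE.* Section {11c} defines compliance for both arms, and {6b} and {20a} are concerned with contamination among controls. No direction follows.
- *Medication changes will be a covariate.* Section {11d} calls a dose change a potential confounder, but {20a} names only unadjusted tests.
- *The shifts amount to 13% to 44% of the planning effect.* This comes from dividing SD units by 0.63 (0.084/0.63 and 0.274/0.63). Under the protocol's own formula the divisor is 0.89.

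**Conclusion.** The point stands in limited form. Section {11d} lets staff who know the allocation decide, without criteria, whether a randomised man continues after a medication change, and its claim that this limits confounding is unsound. The rule conflicts with the commitment in {20a} and {20c} to analyse all men as assigned, because nothing secures the outcomes that such an analysis needs.

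Size and direction are unknown. The 9% to 31% range rests on one-arm removal, exclusion from analysis, assumed removal rates and a trigger correlation of 0.5 to 1.0, none of which the document supplies. If removal were unrelated to outcome, there would be no bias. The wording in {20c} on non-adherence is an ambiguity to clear up, not a second contradiction.

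**What to change.** Replace the case-by-case sentence in {11d} with a statement that a medication change does not end study follow-up: PWV is still measured at weeks 3 and 6, and the man is analysed in his randomised group. Record every change and tabulate changes by arm. Add one sensitivity analysis in which PWV measured after a change is treated as missing, and amend {20b}, which now says that no additional analyses are intended. Delete the claim that the present approach limits confounding.

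As a clarification in {20c}, state that observed values of non-adherent men are kept and that only values actually missing are imputed.

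Decisions about the drugs themselves are not touched. The cost is a short amendment through the route in {25} and one extra analysis; no visits or staff are added, since weeks 3 and 6 are already scheduled. The downside is that the estimated effect will include any effect of medication changes, which the report should say. Recruitment is already under way according to Trial status, and outcomes lost under the present rule cannot be recovered, so the change should be made promptly.
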